### Qualitative methodology: Sampling

This implementation evaluation will be coproduced with academic researchers, national leadership, local services, and patient and carer representatives. It will employ rapid qualitative methods to enable ongoing dissemination of formative learning with participating national and local stakeholders. It will use a multiple-case study design. Case studies permit in-depth analysis of change and its implications within specific contexts, while cross-case comparison (i.e., comparison across multiple case sites) permits identification of both context-specific and cross-cutting lessons on implementation and impact.

To optimise learning, we will sample case sites purposively at organisational and service levels (Table 1) in a range of organisation types (e.g., NHS Foundation Trusts, Teaching Hospitals, District General hospitals), serving different populations in different settings (e.g., large urban area, more rural or mixed geographies). We will study implementation in three contrasting surgical ‘tracer conditions’, varying in terms of urgency/types of options available to patient and clinicians: [1] colorectal cancer surgery (a relatively common and potentially life-threatening surgical condition), [2] repair of abdominal aortic aneurism (prophylactic surgery to address significant risk), and [3] primary knee replacement (elective, non-urgent surgery to address long-term quality of life). Finally, we will sample services at different stages of implementation/uptake, to ensure that we can identify lessons both on common challenges and how services engage with these to progress implementation. NHSE England have provided us with a list of sites (who have consented to be contacted) and an indication of the degree of implementation across the different specialties. Degree of implementation will be one of the variables we consider (in addition to geographical region, type of hospital, etc.) to select the sites included in the study. This variation will help reduce the risk of bias in our sampling.

**Table 1 pone.0335129.t001:** Overview of sampling for service-level case studies.

Dimension	Characteristic	Examples
Organisational	Status	Secondary/tertiary referral centers Unit performs surgery only on local patients
	Population served/ Demographics	Age Gender Ethnicity Socioeconomic status
	Setting	Urban Rural/mixed

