### Quantitative methodology: Effectiveness statistical analysis

The study population is defined to align with the qualitative component of the study. That is, all adults undergoing colorectal cancer surgery, repair of abdominal aortic aneurism or knee replacement at an NHS hospital in England between Jan 1^st^ 2018 and April 1^st^ 2026 in HES APC dataset.

In the absence of randomisation, quasi-experimental research designs are increasingly used for evaluating population health interventions [32,33]. In this analysis, we will use an interrupted times series research design: this method has been widely used to evaluate health interventions with time series data [34].

HES provides a long time series dataset, and, without a control group, a single interrupted time series analysis is the most suitable design to evaluate the programme [35]. We will conduct segmented regression analysis on monthly DAOH measures, postoperative length of stay, rate of emergency re-admission in 30 days,days spent in critical care and also relevant costs [36].

Based on date of surgery, in this analysis we will model monthly data at different time periods between Jan 1st 2018 to Jan 1st 2026, with Jan 2018 to end of Feb 2023 data as baseline period. Intervention period is March 2023 to end of March 2024. Post-intervention period is April 2024 to April 2026.

Specifically, we will model the following:

$$Y_{t}=\;\beta_{\text{0}}+\beta_{\text{1}}T+\beta_{\text{2}}X_{\text{1}t}+\beta_{\text{3}}{(T-T_{i})X}_{\text{1}t}\;+\beta_{\text{4}}X_{\text{2}t}+\beta_{\text{5}}{(T-T_{d})X}_{\text{2}t}\;+\;\varepsilon_{t}$$

Where Yt is the outcome at time t, T represents the time since the start of the study, X_1t_ is a dummy (0/1) variable indicating the intervention period [1] or otherwise 0, X_2t_ is a dummy variable representing the post-intervention period, Ti represents the time point when the intervention starts (X_1t_=1 for T ≥ Ti). Td represents the time point when the post-intervention period starts (X_2t_=1 for T ≥ Td). [37]

$\beta_{\text{0}}$ represents the baseline level of Y at T=0

$\beta_{\text{1}}$ represents underlying pre-intervention trend

$\beta_{\text{2}}$ represents the intercept change immediately following the intervention

$\beta_{\text{3}}$ represents the change in the slope of the trend following the intervention

$\beta_{\text{4}}$ represents the intercept change immediately post the intervention

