$\beta_{\text{5}}$ represents the change in the slope of the trend post the intervention

Details of this methodology are available elsewhere [37].

In our analysis, by stratification, we will examine variations in time trend patterns in geographic location and patients characteristics including age groups, gender, ethnicity and deprivation measured using Index of Multiple Deprivation quantiles. We will use region of residence and local integrated care board in HES data to indicate geographical locations. Age will be grouped as 18–44, 45–65, 66–79, and 80 plus [38]. Ethnicity will be grouped based on ONS 2021 census ethnic categories, including White, Asian and Asian British, Black and Black British, Mixed or multiple ethnic groups, and Other ethnic group. In addition, we will explore variations in NHS hospital sites.

We will also check for seasonality impacts through sensitivity analyses such as using time stratified model, periodic functions or flexible spline functions that are detailed elsewhere [39]. The timing of rollout of the intervention was likely to be different across hospitals, therefore, we will conduct a sensitivity analysis with different definitions of the intervention period (i.e., early implementation period- 1^st^ March to 31^st^ Aug 2023 vs late implementation period – 1^st^ Sep 2023–31^st^ March 2024). Given the dramatic impact of Covid on health services, we will also assess the impact of a shorter baseline period of between Jan 2018 to Feb 2020. In addition, concurrent national programmes that target similar outcomes, such as Getting it Right First Time (GIRFT) [40], could confound our results. We will conduct sensitivity analyses that will stratify by different time periods to adjust for relevant national programmes if there are well-documented dates of implementation and can be distinctly modelled within our time series. We will conduct complete case analyses. Stata 17 (StataCorp) and R 4.2.2 (R Core Team, 2022) will be used to conduct the analysis.

Finally, to examine short-term cancellation, we will conduct descriptive data analysis and describe short-term cancellation data across different time periods and geographical regions.

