The quantitative effectiveness evaluation has several important limitations. First, the study lacks a randomised control group because the early screening programme was implemented nationally across England in all specialties and we only have data for hospitals in England. Without a control group, this makes a single interrupted time series analysis the most suitable approach. Second, the analysis cannot definitively link the intervention to individual patients, relying instead on the timing of the programme’s implementation. This is due to the level of uncertainties around exact timing of the programme’s rollout and differences in pre-existing established early screening and optimisation services across different hospitals in the country. To deal with this, we will conduct several sensitivity analyses using different start dates for the intervention period to account for both early and late implementation and also stratify our analyses by regions or hospitals using results from our short-term cancellation data and qualitative study. Third, this design is susceptible to confounding from co-occurring events and policy changes in the same period. To address confounding events such as in the case of COVID, we will be conducting a sensitivity analysis using a shorter pre-COVID baseline period and by using our qualitative findings to provide context for any observed changes. Fourth, unmeasured confounding may also bias our results. Fifth, the analysis relies on routinely collected hospital data, which may have data quality concerns [43]. To address this, we will conduct thorough data cleaning and preparation to ensure our findings are robust.

We acknowledge that programme success is more complex than simple statistical improvements. It is possible that the programme’s success is demonstrated by widening access to surgery for higher-risk patients who would have been previously excluded, which might result in static or even worsened postoperative complication rates and lengths of stay. To account for this, we will also monitor changes in underlying patient characteristics, such as the percentage of patients in the most deprived quintile of the Index of Multiple Deprivation, which is strongly correlated with multimorbidity rates [44].

Table 4 provides a summary outlining the key components of the study.

**Table 4 pone.0335129.t004:** Summary Table outlining key components of the study.

	Qualitative	Quantitative

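### As written, the effectiveness model combines three contrasting procedures, so a change in procedure mix that departs from the baseline trend can register as a programme effect

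*Protocol article*

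**What the plan says.** All references are to the Protocol article.

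- **Population.** The section on effectiveness statistical analysis takes "all adults undergoing colorectal cancer surgery, repair of abdominal aortic aneurism or knee replacement at an NHS hospital in England" as one study population.
- **Model.** The same section states: "We will conduct segmented regression analysis on monthly DAOH measures". It applies the same approach to length of stay, emergency readmission, critical care days and costs. The equation has an intercept, a baseline trend, and a level and slope term for each of two later periods. Its key reads "Where Yt is the outcome at time t, T represents the time since the start of the study". There is no procedure term or index.
- **Strata.** The plan is that "by stratification, we will examine variations in time trend patterns in geographic location and patients characteristics including age groups, gender, ethnicity and deprivation" (measured by deprivation index). It then adds: "In addition, we will explore variations in NHS hospital sites". Age bands, ethnic groups and geographic units are spelled out. Procedure is not listed.
- **Sensitivity analyses.** These cover seasonality, early and late implementation windows, a January 2018 to February 2020 baseline, and concurrent national programmes. The Discussion adds stratification by region or hospital. None concerns procedure.
- **Case mix.** On the possibility that higher-risk patients gain access to surgery, the Discussion says "we will also monitor changes in underlying patient characteristics, such as the percentage of patients in the most deprived quintile" of the deprivation index.
- **The procedures themselves.** The qualitative sampling section presents them as contrasting, "varying in terms of urgency/types of options available to patient and clinicians". The primary outcome section says DAOH is related to surgical complexity.

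**The concern.** If DAOH depends on surgical complexity, its mean should differ between elective knee replacement, colorectal cancer surgery and aortic repair. A monthly mean over all three then moves whenever their relative volumes move, even if nothing changes within any of them. An uncontrolled interrupted time series treats any departure from the extrapolated baseline as the programme's effect, so the movement lands on β2 to β5, which are the effect estimates.

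The protocol gives reasons to expect the mix to move. It acknowledges a large effect of Covid on services, and that period lies inside the main baseline. Its Introduction also says the programme is meant to identify patients for high-volume, low-complexity hubs, so the mix could shift at rollout itself.

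There is a second cost. A combined series cannot show whether an effect occurred in all three procedures or in one, and the largest group can hide an effect in a smaller one.

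**Working it through.** The protocol states no procedure volumes, mean DAOH, sample size or power, so there is no planned figure to reproduce. Everything below that rests on means or volumes is assumption.

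**1. Simple arithmetic.** Shift in combined mean = change in knee share × gap in mean 30-day DAOH between knee replacement and the other two procedures. Assumed gap: 3 to 8 days.
- 5-point change: 0.05 × 3 = 0.15 day; 0.05 × 8 = 0.40 day.
- 10-point change: 0.10 × 3 = 0.30 day; 0.10 × 8 = 0.80 day.

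**2. The protocol's model fitted to series with no true effect.** Months: 62 baseline (January 2018 to February 2023), 13 intervention (March 2023 to March 2024) and 24 post-intervention (April 2024 to March 2026), 99 in all. Assumed means: 26 days (knee), 21 (colorectal), 20 (aortic). Assumed monthly volumes: 7000, 2000 and 400. The means were constant over time; only knee volume was varied, and there was no noise. The fit was by ordinary least squares.

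| Scenario | Result |
|---|---|
| Constant mix | β2 to β5 all 0 |
| Knee volume grows linearly by 30% over the whole series | β1 = +0.0026 day/month; apparent effect at series end −0.02 day |
| Knee volume rises 20% from April 2024 | β4 = +0.17 day |
| Knee volume falls in the Covid period and is back to its earlier level from March 2023 | β2 = +0.54 day; slope change +0.005 day/month; apparent gain at series end +0.73 day |
| Same Covid fall, baseline limited to January 2018 to February 2020 | β2 to β5 all 0 |

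Hand check of the third row:
- Before: (7000×26 + 2000×21 + 400×20)/9400 = 24.68.
- After: (8400×26 + 2000×21 + 400×20)/10800 = 24.85.
- Difference: 0.17 day, for a knee share moving from 74.5% to 77.8%.

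The values shown for the third and fourth rows are the same whether X1 stays at 1 or returns to 0 in the post-intervention period. Under the second coding, the fourth row also gives β4 = +0.61 day.

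**3. Procedure-specific fit.** Each procedure's mean was held constant, so fitting by procedure, or standardising to a fixed mix, returns exactly 0 for every level and slope change in all these scenarios.

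**4. Masking.** Under the assumed volumes, an effect confined to aortic repair would reach the combined mean at 400/9400 = 4.3% of its size.

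**The case against.** **Pooling is inferred.** The text never says that the procedures will be combined. The statement that "without a control group, a single interrupted time series analysis is the most suitable design to evaluate the programme" concerns the lack of a control and does not show pooling. The equation also serves several outcomes without an outcome index, so it can be read as a template. This stands as a caution on wording. It does not remove the point: there is one population, one model, and a detailed strata list that leaves out the very procedures defining the population.

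**Some detail belongs in an analysis plan that is not shown.** This is fair for covariate lists and comorbidity scores. It is less persuasive for procedure, given how closely the article specifies its age, ethnic and geographic groups.

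**Not every change in mix causes bias.** This is correct. Steady linear drift is almost wholly absorbed by β1. The planned short baseline removes the bias from a Covid dip if the mix has fully returned to its earlier level. But that is a sensitivity analysis, it fails if the return is incomplete, and it does nothing about mix changes during or after rollout. Age, region or hospital strata do not settle the matter either, because mix can shift within each stratum.

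**Stronger readings.** A reader might infer that the estimates will be biased because knee and cancer surgery recovered at different rates. The document gives no volumes or recovery patterns, so it supports only that bias can arise. A reader might also infer that patient-level risk standardisation, including comorbidity, is required. The document does not support that. The Discussion treats wider access for higher-risk patients as a possible success of the programme, so case mix may be partly its result, and screening may itself change how comorbidity is recorded.

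**Conclusion.** The concern holds in a limited form. Followed as written, the plan gives a combined monthly series in which departures of procedure mix from the baseline trend can appear in β2 to β5 as a programme effect, in either direction. None of the listed analyses is designed to separate such a shift from an effect of care. The monitoring of patient characteristics adjusts nothing and does not name procedure.

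The size cannot be derived from the protocol. With an assumed gap of 3 to 8 days, it is 0.15 to 0.4 day of 30-day DAOH per 5 points of knee share. The structural conclusion needs only that mean DAOH differs by procedure, which the protocol's own description of the outcome implies, and that the mix can move off its baseline trend. Whether it did is unknown from this document.

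**What to change.** Make the main analysis procedure-specific: either three separate segmented regressions, or one model with procedure-specific intercepts, trends and effects. Form any overall estimate as an average across procedures with fixed weights set in advance, so that changing volumes cannot move it. Report monthly volume by procedure beside the results, so that readers can see whether and when the mix changed.

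Patient-level risk standardisation can be offered as an optional sensitivity analysis at most, with the unadjusted series alongside.

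The cost is modest. The protocol says HES records procedures, so no new data are needed, and its quantitative timeline already allows for revising the analysis plan while data access is pending. The real downside is wider intervals for the smaller procedure groups.

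### The primary segmented regression has no seasonal term, so an annual cycle can shift its level-change estimates; seasonality belongs in the primary model, not only in a sensitivity analysis

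*Protocol article*

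**What the plan says.** In the protocol article, section Quantitative methodology: Effectiveness statistical analysis, the analysis is announced as "We will conduct segmented regression analysis on monthly DAOH measures", together with length of stay, 30-day emergency readmission, critical care days and costs. One equation follows. It contains an intercept, a linear trend in T, a level and a slope term for the intervention period (X1), a level and a slope term for the post-intervention period (X2), and an error term. Each beta is then defined. No calendar-month, harmonic or spline term appears.

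The periods are fixed as follows:
- Baseline: "with Jan 2018 to end of Feb 2023 data as baseline period".
- Roll-out: "Intervention period is March 2023 to end of March 2024".
- Follow-up: "Post-intervention period is April 2024 to April 2026". The same paragraph also says "we will model monthly data at different time periods between Jan 1st 2018 to Jan 1st 2026", so the last month of the series is not settled.

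Later in the same section: "We will also check for seasonality impacts through sensitivity analyses such as using time stratified model, periodic functions or flexible spline functions". Seasonality is thus a check on the primary result and not part of it.

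On the error term, the article names no distribution, correlation structure, estimator or standard-error method. It refers to a cited source for details of the method. The section Quantitative methodology: Study timeline says that a statistical analysis plan will be revised while data access is pending.

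**The concern.** The conclusions of a single uncontrolled series rest on beta2 to beta5. If hospital outcomes follow a yearly cycle and the model has no term for it, the level and slope terms absorb part of the cycle. What is then reported as a programme effect is partly the calendar position of the cut points: roll-out starts in March 2023 and follow-up starts in April 2024.

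The direction matters too. Suppose, as an assumption, that winter is the worst season, so that days alive and out of hospital (DAOH) reach a trough in January and length of stay peaks in January. The artefact in beta2 would then be a rise in DAOH and a fall in length of stay, both of which read as benefit. A seasonal sensitivity analysis can reveal this, but the shifted figure remains the primary estimate.

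**Working it through.** **No figure to reproduce.** The article gives no standard error, power or effect size for the time series. The check is on how the stated design responds to a yearly cycle.

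**Inputs from the article**
- Baseline January 2018 to February 2023: 5 x 12 + 2 = 62 months.
- Roll-out March 2023 to March 2024: 13 months.
- Follow-up from April 2024: 21 months if the series ends with December 2025, 24 if with March 2026, 25 if with April 2026. All three were run (96, 99 and 100 months).
- T = 0 in January 2018, Ti = 62, Td = 62 + 13 = 75.
- X1 is worded both as 1 in the intervention period only and as 1 for all T at or after Ti. Both codings were run.

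**Assumption.** The cycle is s = A cos(2 pi (T - p)/12), with p the peak month. A and p are not in the article, so results are per unit of A over 12 phases.

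**Bias.** With design matrix X, the omitted cycle adds (X'X)^-1 X's to the estimates.

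| Coefficient | January peak | Largest over 12 phases |
|---|---|---|
| beta2 | -0.67A | 0.87A |
| beta3, per month | +0.105A | 0.12A |
| beta4, X1 period-only | -0.42A to -0.54A | 0.56A to 0.66A |
| beta4, X1 stays at 1 | -1.12A to -1.23A | 1.24A to 1.31A |

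Ranges run over the three series lengths. A January trough reverses every sign. The smallest beta2 shift over the 12 phases is 0.17A.

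**Why the two beta4 rows differ.** If X1 stays at 1, beta4 is measured from the roll-out line extended to T = 75 and not from the baseline line. It therefore equals the period-only beta4 minus (beta2 + 13 x beta3). With 100 months and a January peak: -0.50A - (-0.67A + 13 x 0.105A) = -0.50A - 0.695A, or about -1.20A.

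**Size against the noise.** Under independent errors with standard deviation S, beta2 is the start of a 13-month line minus the baseline line extended to T = 62:
- 13-month line at its first month: 2(2 x 13 - 1)/(13 x 14) = 50/182 = 0.275 S^2.
- 62-month line one month ahead: 1/62 + 12 x 31.5^2/(62 x (62^2 - 1)) = 0.016 + 0.050 = 0.066 S^2.
- Standard error: sqrt(0.275 + 0.066) S = 0.58 S.

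The largest shift is 0.87A/0.58S, about 1.5 x A/S standard errors. The omitted cycle also enters the residuals and raises the model standard errors by a factor of 1.06, 1.22 and 1.73 at A/S = 0.5, 1 and 2 (assumed values). In units of the reported standard error, the largest shift is then about 0.75/1.06 = 0.7, 1.5/1.22 = 1.2 and 3.0/1.73 = 1.7.

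**Cost of the seasonal term.** Adding one sine and cosine pair and comparing the diagonals of the inverse cross-product matrices gives standard errors for beta2 to beta5 about 1% to 4% larger at the same residual variance.

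**Conditional check on serial correlation.** If errors were AR(1) with lag-1 correlation r and the model were fitted with independent errors, the true variance is (X'X)^-1 X'VX (X'X)^-1. Neither r nor the fitting method is in the article.

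| r (assumed) | True / reported SE, beta2 to beta5 | Approximate coverage of a nominal 95% interval |
|---|---|---|
| -0.2 | 0.82 to 0.85 | 98% |
| 0 | 1.00 | 95% |
| 0.1 | about 1.1 | 93% |
| 0.3 | 1.3 to 1.4 | 85% to 88% |
| 0.5 | 1.5 to 1.7 | 74% to 81% |

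**The case against.** The authors have not overlooked seasonality. They commit to examining it, and by the same family of terms recommended here. The dispute is only about which model is primary. The amplitude is unknown and the shift depends on phase: a March or September peak moves beta2 by only 0.17A. All of that is correct, and it limits how strongly the size can be stated. It does not remove the point, because the article does more than stay silent: it writes out the primary mean structure without a seasonal term and places seasonality elsewhere.

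On serial correlation the objection largely succeeds. A reader might infer from the bare error term that months are treated as independent and that the confidence intervals are therefore too narrow. The article does not say so. The same equation could be fitted by least squares, with autoregressive errors or with robust standard errors. Method details are referred to a cited source, and a statistical analysis plan exists but is not shown. The COVID period within a straight-line baseline is a reason to look for runs of same-signed residuals, but it does not establish their size.

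A reader might also infer that the leakage arises because 62 and 13 months are not whole years. That explanation fails. A 60 + 12 + 24 month design gives a larger worst-case beta2 shift, 1.05A against 0.87A. The cause is fitting both a level and a slope to a segment about one cycle long, so moving the cut points would not cure it.

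**Conclusion.** The point holds for seasonality. The primary model as written can give biased level changes: up to 0.87A for beta2, and up to 0.66A or 1.31A for beta4 depending on the coding of X1. This assumes a stable 12-month sinusoid and a fit to the stated equation. Whether the bias matters in practice depends on A, which the article does not give. If A is between half and twice the monthly noise standard deviation, the worst case is roughly 0.7 to 1.7 reported standard errors of beta2.

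Omitting seasonality does not by itself make intervals too narrow. It raises the residual variance and widens the reported standard errors, so the problem is bias.

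On serial correlation the conclusion is conditional only: intervals would be too narrow if independent errors were used and residual correlation were positive. They would be right at zero correlation and too wide if it were negative.

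**What to change.** 1. Add seasonal terms to the primary equation: one or two harmonic pairs, or calendar-month indicators. Keep the model without them as the sensitivity analysis.
2. In the SAP, state that residual autocorrelation will be examined and that autocorrelated errors will be fitted where it is present, for example AR(1) by REML.
3. While editing the equation, settle the coding of X1 and the last month of the series, since the meaning of beta4 depends on the first and its figures on both.

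The cost is one or two sentences and routine code in Stata or R, at a time when the SAP is due for revision anyway. Harmonics use 2 to 4 degrees of freedom and calendar-month terms 11, out of 96 to 100 months. The 1% to 4% widening for one pair is offset to the extent that the seasonal terms reduce the residual variance.

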In 2023, all NHS hospitals in England were asked to implement a programme of early screening, triaging, risk assessment and health optimisation [11]. This included pre-assessment questionnaires and establishing an expanded perioperative care workforce. The directive was published in the 2023/24 NHS Standard Contract [14] followed by guidance published in May 2023 [11].These teams could consist of, for example, care co-ordinators, nurses and perioperative physicians who carry out assessments of health needs to identify surgical risk factors and inform pre- and post-operative care. The team would identify low-risk patients who do not need to attend face-to-face preoperative assessment and patients who could be treated in elective hubs focused on providing High Volume Low Complexity (HVLC) surgery. These services are intended to facilitate early shared decision making and optimisation of patient health, increasing patients’ suitability and readiness for surgery. A key anticipated benefit of these changes is increased safety through reduced perioperative complications (both in terms of complications from surgery, and the psychological harms associated with last-minute cancellations) [11]. The programme may also increase efficiency, e.g., through reductions in last-minute cancellations, reductions in length of hospital stay, and identifying people who can undergo surgery without requiring an overnight hospital stay [11].

The requirement for an early screening, triaging, risk assessment and health optimisation programme (hereinafter referred to as “the programme”) to be implemented was included in the NHS 2023/24 contract with the stipulation that the programme was to be implemented “no later than 31 March 2024”. This is a national programme, with implementation taking place across multiple NHS hospital organisations, in diverse geographic and socioeconomic contexts and within a variety of surgical pathways. It is likely that implementation progressed variably across different clinical and organisational settings. In addition, some settings or specialties (e.g., bariatric surgery) [15] have more well-established multidisciplinary preoperative pathways which aim to optimise comorbidities and reduce the risk of patients undergoing surgery without critical modifiable health issues having been addressed. In this manuscript we describe the mixed methods approach we will adopt to examine the implementation and impact of the new screening programme.

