### Quantitative methodology: Secondary outcomes

The secondary outcomes of this study are postoperative length of stay in hospitals and emergency re-admission within 30 days, as these are related to patient safety in peri-operative setting [29]. Both variables will be constructed using extracted data fields in HES data. In addition, we will examine days spent in critical care [30]. Finally, we will consider related costs using Healthcare Resource Groups (HRG) codes in HES datasets and linking them to the National Tariff.

In addition, we plan to assess the impact of early preoperative screening on the incidence of short-term cancellations by linking data from the Theatre Productivity Dataset with Perioperative Care Census conducted by NHS England [31]. These datasets collect information at the hospital site level, and are currently in their infancy. Data quality and completion will be assessed prior to any analyses to ensure findings are reliable and robust.

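### Region is defined by the patient's residence, but regional strata are also meant to capture rollout of a programme that hospitals deliver; for that use, region should follow the treating hospital

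*Protocol article*

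**What the plan says.** Under Quantitative methodology: Effectiveness statistical analysis, the outcome series are to be stratified by geography and by patient characteristics. Geography is fixed in one sentence: "We will use region of residence and local integrated care board in HES data to indicate geographical locations". Region is therefore by residence. The sentence does not say whether the integrated care board is that of the patient's home or of the provider.

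The other relevant statements concern hospitals:

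- **Delivery.** The Introduction says "In 2023, all NHS hospitals in England were asked to implement a programme of early screening, triaging, risk assessment and health optimisation".
- **Rollout timing.** The statistical analysis section says "The timing of rollout of the intervention was likely to be different across hospitals".
- **Cancellation and census data.** Secondary outcomes says "These datasets collect information at the hospital site level, and are currently in their infancy". The analysis section will nevertheless "describe short-term cancellation data across different time periods and geographical regions".
- **Use of region against uneven rollout.** In the second limitation in the Discussion, the authors respond to uncertain rollout dates and differing pre-existing services by varying the intervention start date, and they will "also stratify our analyses by regions or hospitals using results from our short-term cancellation data and qualitative study".

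The analysis section also plans to explore variation between hospital sites.

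**The concern.** Region serves two purposes in this protocol. In the statistical analysis section it sits beside age, gender, ethnicity and deprivation, as a description of who had surgery and where they live. In the Discussion it is a way of separating areas where the programme arrived at different times or from different starting points. Residence suits the first purpose. For the second, what matters is which hospital screened, optimised and operated on the patient.

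Site-level cancellation data can be placed in a region only through the location of the site. Reading them against HES outcomes grouped by home address compares two different sets of patients under one regional label. Patients who live in one area and are treated in another contribute their outcome to an area whose hospitals did not treat them. A finding of little regional variation in level or slope change could then partly reflect the grouping rather than the programme. The Discussion's list of limitations does not mention this.

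**Working it through.** The protocol gives no figure for this point, so there is nothing to reproduce. The check has two parts.

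**1. The statements side by side**

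| Item | Unit | Where stated |
|---|---|---|
| Region for HES outcomes | Patient's residence | Effectiveness statistical analysis |
| Integrated care board | Residence or provider not stated | Effectiveness statistical analysis |
| Delivery of the programme | Hospital | Introduction |
| Variation in rollout timing | Hospital | Effectiveness statistical analysis |
| Cancellation and census data | Hospital site | Secondary outcomes |
| Strata used against uneven rollout | Regions or hospitals, informed by cancellation and qualitative results | Discussion |

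The only definition of region in the article is by residence, and nothing says how it is matched to site-level data. If the Discussion's regions are by residence, they do not match the cancellation data. If they are by provider, they depart from the definition in the methods. Either way the two places need to be reconciled.

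**2. Illustration of the dilution**

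Inputs, all assumed:

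- c is the share of an area's residents treated in another area. The protocol does not give it; 1% to 30% is shown.
- The programme effect belongs to the treating hospital's area.
- Crossing is unrelated to outcome.
- K is the number of areas; nine is illustrative.

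Let D be the true difference in effect between two areas, with effects A and B.

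- *Two areas, symmetric flow.* Residents of the first average (1−c)A + cB, and residents of the second (1−c)B + cA. The difference is (1−2c)D.
- *Two areas, one-way flow.* (1−c)A + cB − B = (1−c)D.
- *K areas, crossers spread evenly over the others.* The own-area weight is 1−c and each other area has weight c/(K−1). The difference is [1 − c − c/(K−1)]D = [1 − cK/(K−1)]D.

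Share of the true contrast kept when grouping by residence:

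| c | Two areas, symmetric | Two areas, one-way | Nine areas |
|---|---|---|---|
| 1% | 0.98 | 0.99 | 0.99 |
| 5% | 0.90 | 0.95 | 0.94 |
| 10% | 0.80 | 0.90 | 0.89 |
| 20% | 0.60 | 0.80 | 0.78 |
| 30% | 0.40 | 0.70 | 0.66 |

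For example, nine areas at c = 10% give 1 − 0.10 × 9/8 = 0.8875. Grouping by the treating hospital's area gives 1.00 by construction, meaning no dilution from this source.

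**The case against.** The case on the other side has considerable force.

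- **Residence is a proper choice for what the methods section describes.** Geography is listed there with demographic characteristics, and that section does not call it a proxy for exposure. This stands: the point concerns only the use of region for rollout or alongside cancellations.
- **A hospital-based route already exists.** Hospital-site variation is to be explored, the Discussion says regions or hospitals, and Integrated approach adds a case study of implementation maturity at the five sites. This is real mitigation. It does not repair the regional strata, but it does show that hospital identity is needed anyway.
- **The Discussion may already mean provider regions, and the analysis plan is still to be revised.** Possibly so, but the article fixes a residence definition and gives no other. This is a stated choice, not merely an omitted detail.
- **The size is not established.** This stands. No crossing share is documented, and 1−2c applies only to two areas with symmetric exchange. Table 1 distinguishes units by referral status ("Secondary/tertiary referral centers Unit performs surgery only on local patients"), but it is a qualitative sampling frame and gives no evidence of patient flows in the HES cohort.
- **Grouping by provider has its own cost.** The Introduction says the programme identifies patients who could be treated in elective hubs. Place of treatment may therefore change because of the programme and shift case mix between provider-based areas over time; residence is not altered by that. This also stands and shapes the fix.

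A reader might infer that all the geographic strata are wrong, or that regional results are certain to be biased towards no variation. The documents support neither. The integrated care board is not clearly residence-based, and if patients who cross differ in risk, the bias need not be towards zero.

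**Conclusion.** The point holds in a limited form. When region represents programme rollout, or is compared with site-level cancellation data, the residence definition misassigns patients treated outside their home area. Dilution of between-area differences is the expected direction if crossing is unrelated to outcome.

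Its size cannot be estimated from the protocol. It could be negligible for large regions, and the tabulated ratios are illustrations under assumed crossing shares, not estimates for this cohort.

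A reader might also take this as a threat to the main result. It is not: the national interrupted time series pools all of England, so where a patient is placed within England does not enter it. This is a minor point about secondary stratified analyses, worth settling before the data arrive.

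**What to change.** In the geographic stratification paragraph of the statistical analysis section, and in the second limitation of the Discussion:

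1. Assign region and integrated care board by the treating hospital site for any stratum that represents programme rollout or is compared with the cancellation data, including the regional description of cancellations.
2. Keep residence for descriptive geography, deprivation and equity strata, and state for each use of the integrated care board which assignment applies.
3. Report the share of patients treated outside their area of residence, by tracer procedure if possible, so that readers can see whether the choice matters.
4. Show the residence-based result beside the provider-based one, because redirection to elective hubs may change case mix in provider-based areas over time.

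The cost is a few sentences and one additional set of tables. Hospital identity is already needed for the planned hospital-site analysis, and Quantitative methodology: Study timeline already sets aside time to revise the analysis plan while data access is pending.
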